**5. Ethics**

**5.1 Consent:**

Patients who have undergone an abortion may not wish to be contacted following the procedure for very personal reasons. Since the main focus of the study is to provide follow up to these women to facilitate contraceptive uptake and continuation, we plan to engage these women by obtaining a fully informed consent at the start of the study.

**5.2 Confidentiality:**

Patients will be given unique identifiers on entry to the study. To enable us to follow them up at 1 and 2 years to examine the repeat abortion rate without having to re-contact the patient, routinely collected data from the Public Health Department in Lambeth and the Department of Health will be matched to our research data using initials, date of birth and post codes. The link between the unique patient identifier and patient details will be maintained within a secure password protected NHS database, using all current guidelines employed by King’s College NHS Foundation Trust. Only NHS encrypted memory sticks will be used for data transfer. Once the database is locked at the end of the study period (3 years) all links will be destroyed by removing initials, dates of birth and postcodes from the study data.

**5.3 Vulnerable clients :**

**1) Victims of sexual assault:**

Victims of sexual assault undergoing an abortion will be included in the study as these women may benefit from specialist contraceptive support following their abortion and research information about the effect of any intervention to prevent future unplanned pregnancies in this group will be useful. In the event of disclosure of sexual assault, patients will also be offered a referral to dedicated Specialist services for victims of sexual assault for additional support.

**2) Under 16 year olds:**

We decided to include under-16’s in this study as they are a vulnerable group with a high abortion rate and research information about the effect of any intervention to prevent future unplanned pregnancies in this group is crucial. All under-16’s participating in the study will be assessed for Fraser competence before being given advice and treatment. They will also be assessed to explore any child protection issues that may arise and will be referred to the Safeguarding Children team as may be required. All clinicians involved in the research team are trained in Child protection procedures.

**3) Those who do not speak English:**

We have excluded non-English speaking patients from our study due to the logistics of obtaining informed consent and providing telephone follow-ups.

**4) Patients who lack capacity to consent for themselves:**

These patients will be excluded from the study.

### 6 Statistics

### 6.1 Sample Size

| A stratified design, which divides the sample among 6 strata (3 centres, 2 arms in each centre), is analyzed using the two-sided, Cochran-Mantel-Haenszel test. Sample sizes, summed across all strata, of 223 in intervention group and 223 in control group achieve 95% power and 0.05 significance to detect a difference of 15% in the percentage of women using LARC (Long- acting methods of reversible contraception such as injectables, implant or intrauterine device) or contraceptive pills in each group at 6 month follow-up. Allowing for 65% accepted participation rate and 60% follow-up rate, we require a total of 1144 patients across the three centres: 618 patients from BPAS, 366 from MSI and 160 patients from King’s College Hospital.    **Randomisation**: centre-stratified block randomization  **Primary outcome:** contraceptive uptake at 6months  **Secondary outcome:** repeat abortion rate at 1 year and 2 years  **Sample size calculation:**  Based on abortion data for Lambeth, Southwark and Lewisham residents in 2009, there were 2885 NHS abortions in BPAS, 1725 in MSI and 748 in King’s College Hospital. From this data, we can deduce the average of number of abortions at 3 months as: 721 (54%) abortions in BPAS, in 431 (32%) MSI and 187 (14%) in Kings with a total number of abortions for all the 3 centres estimated as 1339. It is anticipated that recruitment could be completed in 4-6 months.  Based on published papers (Schunmann et. Al [21]), there was 68% uptake of LARC or contraceptive pills at 4months following abortion; we have assumed the same at 6months post-abortion. 34.84% refused to participate in the above study; We have used 35 % refusal to participate for sample size calculation. There was 61.5% follow-up rate at 4months in the above study. We have used 60 % follow-up rates at 6 months. |
| --- |

**6.2 Randomisation**

| Please refer to section 3.4 |
| --- |

**6.3 Analysis**

**Statistical analysis of primary outcome:** comparison of the binary outcomes (rates) in the two arms and adjusting for centres using Cochran-Mantel-Haenszel test.

**Statistical analysis of Secondary outcome**: comparison of the proportions (rates) in the two arms, Chi2 test, logistic regression and time-to-event analysis.

|  |
| --- |

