### 3.5 Withdrawal of Subjects

### Patients will be free to withdraw from the study anytime they wish. Baseline data collected on these subjects will be used for the analysis.

### 3.6 Expected Duration of Trial.

| Expected clinical participation of patients in the study will be for a period of 6 months. The total duration of the study will be 2-3 years to complete analysis of the secondary outcome of repeat abortions at 2 years. |
| --- |

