**15. Appendices**

**15.2 Appendix 2: Topic Guides for data collection**

1. **Topic Guide for baseline data collection at recruitment**: (This will be collected for both the ‘Control’ and ‘Intervention’ groups)

- Date of Birth
- Ethnicity
- Post code
- Educational achievement
- Marital/Relationship status
- Parity
- Previous abortions
- Contraceptive use immediately prior to current pregnancy
- Planned method of contraception after abortion
- Who referred for the abortion : Self/GP/Family Planning or Sexual Health clinic/other

1. **Topic Guide for Data collection at the 2-4 week consultation with the Specialist in Reproductive and Sexual Health:** (This is for the ‘Intervention’ Group only)

- Any change in the relationship status
- Whether accompanied by partner for this visit (if having a face-face consultation in a clinic)
- Smoking
- Alcohol use
- Drug misuse
- Domestic violence
- Relevant Medical History
- Any physical problems following the abortion
- Level of psychological distress following abortion
- Any additional psychological support required
- Any concerns about future fertility
- Any unprotected sexual intercourse since the last abortion
- Any use of Emergency contraception since the last abortion
- Contraceptive method provided at the time of abortion
- Current method of contraception
- When was the method started
- Is the contraceptive method being effectively used
- Any side-effects from the contraceptive method
- Any particular method of contraception medically contraindicated
- Previous contraceptive use
- Any problems with previous contraceptive methods
- Any particular contraceptive method/s unacceptable to the patient
- Attitude to future unplanned pregnancy
- Awareness of safer sex practice, STIs
- Contraceptive method provided at this visit
- Arrangements for Follow up
- Any referral to other agencies/other Healthcare professionals:
- Social services
- Safeguarding children team
- Safeguarding adults team
- Domestic violence support
- Alcohol and Drug misuse
- Mental Health team
- Psychologist
- Health advisor/counsellor
- Haven
- Services for trafficked women
- Support services for women working in prostitution
- General Practitioner

1. **Topic Guide for the phone call to study participants who DNA the 2-4 week appointment** (This is for the Intervention group only)

- Reason for DNA
- Offer suitable alternative appointment (telephone consultation or face-face clinic appointment) as preferred by the patient

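### The primary analysis adjusts for centre only and, as sized, compares only the women reached at 6 months; prespecified baseline adjustment and a missing-outcome sensitivity analysis would improve it at little cost

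*Protocol*

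**What the plan says.** Section 6.3 names one primary analysis: "comparison of the binary outcomes (rates) in the two arms and adjusting for centres using Cochran-Mantel-Haenszel test". Logistic regression and time-to-event methods appear there for the secondary outcome only.

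Section 6.1 uses the same test; the stratified design "is analyzed using the two-sided, Cochran-Mantel-Haenszel test". Sample sizes "of 223 in intervention group and 223 in control group" are said to "achieve 95% power and 0.05 significance to detect a difference of 15" percentage points. The control rate comes from a published trial in which "there was 68% uptake of LARC or contraceptive pills at 4months following abortion". The 446 are then inflated for 35% refusal and for loss: "We have used 60 % follow-up rates at 6 months". The 446 are therefore the women with a 6-month outcome.

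Topic Guide A in Appendix 2 collects date of birth, previous abortions, contraceptive use before the pregnancy and "Planned method of contraception after abortion" in both arms.

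Section 3.5 says of women who withdraw: "Baseline data collected on these subjects will be used for the analysis". It does not say which analysis.

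Sections 2.2 and 2.3 give the intervention arm a call in the week after the procedure, a specialist consultation at 2-4 weeks and a call at 3 months. The study first contacts controls after the abortion at 6 months.

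**The concern.** Two features of the stated analysis deserve attention.

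First, variables that could plausibly predict contraceptive use at 6 months are collected on everyone before the intervention but play no part in the primary comparison. A covariate that explains some of the outcome buys precision without recruiting anyone.

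Second, about 40% of consenting women are expected to have no primary outcome, and contact before that point differs sharply by arm. A woman who has already spoken to the team up to three times may be easier to reach at 6 months, or more tired of calls, and either tendency may depend on whether she is using contraception. Randomisation balances everyone randomised; it does not balance those who answer. If response depends on the outcome differently in the two arms, the comparison of responders can show a difference where there is none, or hide a real one.

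Section 3.5 adds an ambiguity. Baseline data from withdrawn women are to be used, but a CMH table of observed 6-month outcomes, as section 6.3 stands, gives them no place.

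**Working it through.** **Inputs from the protocol.** Control rate 68%; difference 15 points, so intervention 83%; two-sided alpha 0.05; power 95%; 223 per arm with an outcome; 65% participation; 60% follow-up (all section 6.1).

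**1. Reproducing the plan's figures.** The two-proportion formula for 68% v 83% gives 211 per arm without continuity correction and 224 with it, against the stated 223. Simulating the three-centre CMH test (54/32/14% split) at 223 per arm gives power 0.962 without correction and 0.951 with it. Inflation: 446 / 0.65 / 0.60 = 1143.6, hence 1144. The sample size holds.

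**2. Who is in the comparison.** Consenting: 1144 × 0.65 = 743.6. Reached: 743.6 × 0.60 = 446.2. Without a primary outcome: about 297, or 40%.

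**3. Gain from adjustment.** The protocol gives no strength for any predictor, so the share of outcome variance explained (R²) is assumed. Effective n per arm = 223 / (1 − R²).

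| Assumed R² | Effective n per arm | Power, 68% v 83% |
|---|---|---|
| 0 | 223 | 0.960 |
| 0.05 | 234.7 | 0.968 |
| 0.20 | 278.8 | 0.986 |

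The gain is about 1 to 3 points of power.

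**4. Possible bias from differential response.** Suppose there is no true effect and both arms have 68% users. Let r_u and r_n be the assumed response rates of users and non-users. The rate observed among responders is 0.68 r_u / (0.68 r_u + 0.32 r_n).

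- Intervention, 70% and 50%: 0.476 / (0.476 + 0.160) = 0.748; overall response 63.6%.
- Controls, 60% and 60%: 0.680; overall response 60%. Spurious difference 74.8 − 68.0 = +6.8 points. At 223 per arm, a two-sided 5% test rejects in about 36% of trials.
- Controls, 60% and 50%: 0.408 / (0.408 + 0.160) = 0.718; overall response 56.8%. Spurious difference 74.8 − 71.8 = +3.0 points; rejection about 11%.

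Both scenarios give overall response near the planned 60%. The direction is not known: exchanging the arms' response rates reverses the sign.

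**5. What the missing 40% could do to a result on target.** Suppose 83% v 68% is observed with 40% missing in each arm. Without assumptions about the missing women, the difference among all randomised lies between 0.6 × 83 − (0.6 × 68 + 40) = −31 and (0.6 × 83 + 40) − 0.6 × 68 = +49 points. If only the missing intervention women differ, with a rate 10 or 20 points below those reached, it is 15 − 0.4 × 10 = 11 or 15 − 0.4 × 20 = 7 points.

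**The case against.** The main objection is that nothing in section 6.3 is wrong. CMH stratified by centre, the randomisation factor, is a valid test, agrees with section 6.1 and already has the planned power. Adjusting for further covariates is a choice of efficiency, worth 1 to 3 points. That stands, and it sets the weight of the point.

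Covariate lists and missing-data methods are also commonly left to a statistical analysis plan, which is not shown. That stands too: their absence from the protocol is not a finding. What remains is that the protocol fixes a primary method and sizes it on women reached, and a better method is available with data already being collected.

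The bias example makes response depend on the outcome itself. Imputation from baseline variables removes such bias only so far as those variables explain the dependence; with R² of 5-20%, much could remain. This is why a tipping-point analysis belongs beside the imputation.

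A reader might infer more than the protocol supports:

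- That the baseline variables are strong predictors, or predict being reached. No figure says so; the Background lists risk factors for repeat abortion, a different outcome.
- That withdrawn women's baseline data cannot be used. They could serve in description, in comparing women reached with those not reached, or in imputation followed by CMH.
- That a woman who stops taking calls counts as withdrawn and leaves the linked outcome. Section 3.5 does not say this, and sections 5.2 and 11 design the linkage to work without further contact.
- That 40% will withdraw. The 40% is loss to follow-up; no withdrawal rate is given.

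**Conclusion.** The point holds as an improvement in efficiency and robustness, not as the correction of an error. The power gain is modest: about 96% to 97-99%, assuming the four covariates explain 5-20% of outcome variance. The larger reason to act is the expected 40% without an outcome combined with study contacts before 6 months in one arm only. Illustrative response rates give a false difference of 3 to 7 points, up to nearly half the 15-point target. Those rates are assumptions; the protocol offers nothing to show that such a pattern will occur, or in which direction. Section 3.5 is vague beside section 6.3 and needs clarifying, but it does not contradict it outright.

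**What to change.** - **Primary analysis (6.3).** Prespecify a logistic regression with arm, centre, planned method, contraceptive use before the pregnancy, previous abortions and age. Report a standardised risk difference with 95% CI, the scale of the 15-point target. Keep the centre-stratified CMH test as a supporting analysis.
- **Sensitivity analysis.** Multiply impute the outcome of women not reached, by arm, from the baseline variables. Add a tipping-point analysis that varies the assumed rate among women not reached, separately by arm, because imputation from baseline cannot remove outcome-dependent non-response.
- **Linked data.** Do not make the primary result depend on linked 1-2 year abortion data. They arrive later, and national linkage is only to be attempted, subject to permission (section 4, study end points).
- **Withdrawal (3.5).** State that all data collected up to withdrawal are kept, and name the analyses they enter. State that women who only stop taking calls stay in the linkage-based secondary outcome unless they withdraw consent for linkage. Check this against the consent form.

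The cost is revised wording, modest extra programming and a record of what each withdrawing woman withdraws from. Neither new participant data nor a change in sample size is needed.

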### Participants will be randomised by predetermined codes for each centre (strata) to intervention or control arm. The Randomisation list will be prepared by the Research statistician with a computer generated random number list stratified by centre and with random block sizes. The randomisation schedule will be incorporated into a dedicated electronic database and kept securely within this electronic system, inaccessible to the enrolment location. The allocation sequence will be concealed from the person enrolling and assessing participants to the study. The consent forms will be sent to the Chief Investigator based at King’s College Hospital at the end of each week. Participants will be assigned to the intervention or control arms based on the randomisation codes embedded within the dedicated electronic database system.

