**4. Study Procedures**

**4.1** Patient Information (Appendix 1):

Patient Information Sheet will be sent by Central TOP Booking Service when patients ring for their abortion appointment, after obtaining verbal consent for receiving information by post. Patients who decline postal contact will be given the information sheet when they attend for their abortion consultation.

**4.2**  Screening and eligibility:

Screening and Recruitment will be done by a member of the research team or a member of staff from the TOP Provider Unit when patients attend for their abortion consultation, after their abortion consultation.

**4.3** Baseline Assessment:

Patients approached for participation about the study will be requested to fill in a questionnaire (Appendix 2: Topic Guide A) to collect baseline socio-demographic and other relevant data relating to their sexual, reproductive and contraceptive history.

4.3(a) Retrospective data collection

Following minor amendment to the protocol (approved by NRES on 7th June 2013) we plan to collect retrospective data on abortions within the 2 years prior to recruitment in study participants. This data will allow us to better understand the contraceptive trajectories and potential future risk of repeat abortion in our recruited cohort. We will be obtaining this data through data linkage with the National abortion dataset held at the Department of Health.

**4.4** Informed Consent:

Written consent on a Consent form (Appendix 1) will be obtained from patients who are willing to participate in the study.

**4.5** Randomisation:

Patients will be randomised by predetermined codes for each centre (strata) to the intervention arm and control arm. The Randomisation list will be prepared by the Research statistician with a computer generated random number list stratified by centre and with random block sizes and held in a dedicated electronic database. The randomisation schedule will be inaccessible to the enrolment location. Patients will be allocated to the Intervention or Control arms based on the randomisation codes for each centre.

**4.6** Intervention:

1) Follow up consultation by telephone/face-face clinic appointment as per the patient’s preference with a Specialist from the Reproductive & Sexual Health Service at King’s College Hospital 2-4 weeks post-abortion. Women will be offered the opportunity to bring their male partners to the follow-up appointment if they wished, for participation in contraceptive counseling.

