Effective contraception will be defined as regular and consistent use of oral contraceptive pills/patches/vaginal ring (Nuvaring®)/ injectable contraception/ intrauterine contraception or the contraceptive implant. Use of barrier contraception or other methods such as withdrawal methods or natural family planning will not be considered as effective contraception due to their higher relative failure rate.

At 6 months post-abortion, the Research nurse/Fellow will contact patients in both intervention and control arms to assess contraceptive uptake and continuation. Data will be collected using a standardized questionnaire (Appendix 2: Topic Guide E) to explore factors that could have potentially influenced contraceptive decision-making, compliance and continuation. Information will also be obtained about the number of contacts patients in both groups have had with Health Care professionals relating to contraception since their abortion.

- **Repeat abortion at 1 and 2 years**

Anonymised data using unique patient identifiers such as Date of Birth and post code will be used to identify the proportion of study participants in each arm undergoing a repeat abortion within 1 year and 2 years following their abortion. This data will be obtained from the data routinely collected by the Public Health Department in Lambeth from the three abortion provider units for Lambeth, Southwark and Lewisham. It is possible that a small proportion of the study participants may have moved outside the boroughs of Lambeth, Southwark and Lewisham over a period of 2 years following their abortion and may have presented elsewhere for their repeat abortion. The Department of Health routinely collects statutory data returns from all abortion providers in England and Wales on all legal abortions. We will attempt to obtain permission from the Department of Health for Data linkage with the national abortion dataset for more complete information on repeat abortion rates in our study participants.

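### Repeat abortion is compared with a plain chi-square test although randomisation is stratified by centre and the primary analysis adjusts for it: a small, free improvement

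*Protocol*

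**What the plan says.** Protocol section 6.3 has one sentence for each outcome. The primary outcome, effective contraception at 6 months, is compared between arms "adjusting for centres using Cochran-Mantel-Haenszel test". Section 6.1 agrees: the stratified design "is analyzed using the two-sided, Cochran-Mantel-Haenszel test".

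The secondary outcome is the "repeat abortion rate at 1 year and 2 years" (section 6.1). The endpoint text in section 4 defines it as the proportion in each arm "undergoing a repeat abortion within 1 year and 2 years following their abortion", so the two time points are nested. Its analysis is given as "comparison of the proportions (rates) in the two arms, Chi2 test, logistic regression and time-to-event analysis". Centre is not mentioned, and neither a leading method nor a leading time point is named.

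Both outcomes come from the same allocation, a "computer generated random number list stratified by centre and with random block sizes" (section 3.4).

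**The concern.** Stratifying by centre with blocks balances the arms within each centre. If centres differ in repeat-abortion risk, part of the outcome variation is between centres, and the design has removed that part from the comparison of arms. A chi-square test on the pooled two-by-two table still counts it in the standard error. The standard error is then slightly too large, the test rejects too rarely under no effect, and some power is lost.

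The protocol avoids this for the primary outcome and, in the next sentence, names a test with no centre term for the secondary one. Repeat abortion is part of the study objective (section 2.1), and section 1 links the findings to policy on reducing it. The trial is sized on 6-month contraception alone, so power for repeat abortion is whatever the sample happens to give. A method that costs nothing and recovers a little of it is worth having.

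**Working it through.** **The plan's own figure.** For the primary outcome, 68% against an assumed 83% (68% plus 15 points), two-sided 0.05 and 95% power, the continuity-corrected two-proportion formula gives 224 per arm. The protocol states 223. Inflation: 446 / 0.60 / 0.65 = 1143.6, stated as 1144. The primary sizing therefore reproduces. There is no corresponding figure for repeat abortion.

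**Inputs for the check**
- Centre shares 54%, 32% and 14% (section 6.1).
- Women per arm: 1144 × 0.65 / 2 = 371.8, taken as 372. This assumes that 1144 are approached, 65% take part, and linkage covers all who are randomised.
- Repeat-abortion rates: not in the protocol. Assumed 2-year rates by centre are 25/10/5% (strongly different) and 15/12/10% (similar).

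**Size of the plain test.** Let w be the centre share, p the centre rate and P = Σwp. The pooled test uses variance P(1−P). Under centre-balanced allocation the variance that applies is Σwp(1−p). The effective critical value is 1.96 × √[P(1−P) / Σwp(1−p)].

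*Centres 25/10/5%*
- P = 0.135 + 0.032 + 0.007 = 0.174, so P(1−P) = 0.1437.
- Σwp(1−p) = 0.10125 + 0.0288 + 0.00665 = 0.1367.
- Critical value = 1.96 × √(0.1437/0.1367) = 2.010, which gives a two-sided size of 4.4%.

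*Centres 15/12/10%*
- P = 0.1334, P(1−P) = 0.1156, Σwp(1−p) = 0.1152.
- Critical value = 1.963, size 4.96%.

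**Power with centres 25/10/5%, intervention 4 points lower in each (21/6/1%)**
- Rates averaged over arms are 23/8/3%. Overall 0.154, pooled variance 0.1303, within-centre variance 0.1233.
- Standard error: pooled √(2 × 0.1303/372) = 0.02647; stratified √(2 × 0.1233/372) = 0.02574.
- Actual standard error of the difference: √[(0.1367 + 0.1090)/372] = 0.02570.
- Plain test: Φ[(0.04 − 1.96 × 0.02647)/0.02570] = 32.2%.
- Stratified test: Φ[(0.04 − 1.96 × 0.02574)/0.02570] = 34.2%.

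**Simulation agrees**

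| Assumed centre rates | Quantity | Plain chi-square | CMH |
|---|---|---|---|
| 25/10/5% | size | 4.6% | 5.0% |
| 25/10/5%, 4-point effect | power | 32.2% | 34.2% |
| 15/12/10%, 5-point effect | power | 59.2% | 59.7% |

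These used 20,000 trials per row. A separate run gave 4.5% against 5.0% for size and 32.4% against 34.6% for power in the 25/10/5% case, and no material difference with similar centres.

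**Two nested time points.** Under no effect, the test statistics for the cumulative proportions p1 (1 year) and p2 (2 years) have correlation √[p1(1−p2) / (p2(1−p1))]. The chance that at least one exceeds 1.96 in absolute value follows from the bivariate normal distribution.

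| Assumed p1, p2 | Correlation | At least one p<0.05 |
|---|---|---|
| 5%, 10% | 0.69 | 8.4% |
| 8%, 15% | 0.70 | 8.3% |
| 10%, 20% | 0.67 | 8.5% |

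Simulation (4,000 null trials per scenario, 2-year rates 10–15%) gave 7.2–8.7% for the two chi-square tests. Adding a log-rank test gave 7.3–8.8%, an increase of 0.1 to 0.2 points. Logistic regression was not simulated.

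**The case against.** The strongest reply is that this rests on silence in a short protocol section. Centre terms, covariates, the lead method and the handling of two time points for a secondary outcome are commonly left to a SAP, which may exist and is not shown. Logistic regression and time-to-event analysis can both include or stratify by centre. The plain test is valid, the gain is at most about 2 points of power under an assumed and rather extreme spread between centres, and the protocol claims neither power nor a significance level for this outcome.

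Most of that stands. It makes the point minor and removes several stronger readings:

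- A reader might infer that the whole secondary analysis ignores the strata. The text does not say so; it is silent on centre for the two models.
- A reader might infer that listing three methods drives up false positives. The calculation shows that the two time points account for almost all of the inflation. Even that figure applies only if success is claimed on whichever test is significant, which the protocol never says.
- A reader might infer that earlier abortions should have been a covariate, because section 4.3(a) says "we plan to collect retrospective data on abortions within the 2 years prior to recruitment in study participants". The purpose given there is to understand the recruited cohort, with no commitment to adjustment. Leaving the covariate unnamed contradicts nothing.

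What survives is that section 6.3 does not simply defer to a later plan. It names a chi-square test, which has no centre term, beside a primary analysis that has one. That is a stated method, and a better one of the same kind is already in the protocol.

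**Conclusion.** The point holds as a minor improvement to a stated method. The test named for repeat abortion does not use the centres by which women are randomised, while the primary analysis does. A reader might take this as an error that invalidates the comparison; it is not, since size stays at or below about 5%.

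The cost is a slightly conservative test: size about 4.5% and about 2 points of power with centre rates of 25/10/5%, and under 1 point with 15/12/10%. Both sets of rates, and 372 women per arm, are assumptions. The true cost depends on how far the three centres differ, which the protocol does not report.

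The lack of a leading method and time point is a secondary matter that a SAP could settle. The chance of about 8% of at least one nominally significant result holds for assumed 2-year rates of 10–20%.

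**What to change.** In section 6.3, replace the plain chi-square test for repeat abortion with a CMH test stratified by centre. Report the Mantel-Haenszel risk difference with its 95% CI at 1 and 2 years. State that the logistic model includes centre and that the time-to-event analysis includes or is stratified by centre.

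Optionally, add one sentence naming a single method and time point as leading and labelling the others supportive. If a SAP exists, align it with this wording.

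The cost is one or two sentences. Centre is known for every woman from the randomisation, and repeat abortions come from the linkage already planned, so the change needs no extra data and no change in sample size.
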